## Abstract

**Background:**

The quality of warfarin anticoagulation among Sub-Saharan African patients is suboptimal. This is due to several factors, including a lack of standardized dosing algorithms, difficulty in providing timely international normalized ratio (INR) results, a lack of patient feedback on their experiences with treatment, a lack of education on adherence, and inadequate knowledge and training of health care workers. Low quality of warfarin anticoagulation, expressed as time in therapeutic range (TTR), is associated with higher adverse event rates, including bleeding and thrombosis, and ultimately, increased morbidity and mortality. Processes and interventions that improve this situation are urgently needed.

**Objective:**

This study aims to evaluate the implementation of the “warfarin bundle,” a package of interventions to improve the quality of anticoagulation and thereby clinical outcomes. The primary outcome for this study is TTR over the initial 3 months of warfarin therapy.

**Methods:**

Patients aged 18 years or older who are newly initiated on warfarin for venous thromboembolism, atrial fibrillation, or valvular heart disease will be enrolled and followed up for 3 months at clinics in Cape Town, South Africa, and Kampala, Uganda, where the warfarin bundle is implemented. A retrospective review of the clinical records of patients on warfarin treatment before implementation (controls) will be used for comparison. This study uses a mixed methods approach of the implementation of patient- and process-centered activities to improve the quality of anticoagulation. Patient-centered activities include the use of clinical dosing algorithms, adherence support, and root cause analysis, whereas process-centered activities include point-of-care INR testing, staff training, and patient education and training. We will assess the impact of these interventions by comparing the TTR and safety outcomes across the 2 groups, as well as the cost-effectiveness and acceptability of the package.

**Results:**

We started recruitment in June 2021 and stopped in August 2022, having recruited 167 participants. We obtained ethics approval from the University of Cape Town Faculty of Health Sciences Human Research Ethics Committee, the Provincial Health Research Committees in South Africa, the Joint Clinical Research Centre Institutional Review Board, Kampala, and the University of Liverpool Research Ethics Committee. As of February 2023, data cleaning and formal analysis are underway. We expect to publish the full results by December 2023.

**Conclusions:**

We anticipate that the “bundle of care,” which includes a clinical algorithm to guide individualized dosing of warfarin, will improve INR control and TTR of patients in Uganda and South Africa. We will use these findings to design a larger, multisite clinical trial across several Sub-Saharan African countries.

**International Registered Report Identifier (IRRID):**

DERR1-10.2196/46710

## Introduction

### Background

Oral anticoagulation is vital for several diseases that are prevalent and increasing in Sub-Saharan Africa (SSA). Warfarin remains one of the most frequently used oral anticoagulants, particularly in lower-resource settings, such as SSA [1], but is difficult to use because of its narrow therapeutic index, wide variability in individual daily dose requirements required to achieve the desired effect and need for frequent monitoring. Achievement of the target international normalized ratio (INR) is critical to prevent the recurrence of thrombosis and bleeding. Several studies have described low time in therapeutic range (TTR) [2]. In our previous study, our own cohorts in Uganda and South Africa demonstrated a TTR of 41% [3] compared to TTRs of up to 70% in high-income settings [4].

We identified several reasons that contributed to this low quality of anticoagulation, including a lack of standardized dosing algorithms with different practices in different clinics, difficulty in providing INR results at the time patients attend clinic, a lack of patient feedback on their experiences while on treatment and education on adherence, inadequate knowledge and training of health care workers, a lack of standardization of quality improvement procedures, and the lack of availability of different dosage strengths of warfarin tablets.

A simulation study [5] in the United States suggested that improving TTR by 5% resulted in a 7.2% reduction in all adverse events in a population of 67,070 patients anticoagulated for atrial fibrillation over a 2-year period. This included 183 ischemic strokes, 269 major hemorrhages, and 662 deaths. Increasing TTR by 5% saved US $15.9 million and gained 863 quality-adjusted life years (QALYs) during this period [5]. In our population, with a median TTR of 41% [3], an improvement in TTR would be expected to have a greater impact since the relationship between TTR and mortality is nonlinear.

We aim to introduce a package of measures using a mixed methods approach, which we have termed the “warfarin bundle,” in anticoagulation clinics in 2 cities (Cape Town, South Africa, and Kampala, Uganda), to improve the quality of anticoagulation. The bundle includes patient-centered and process-centered activities, namely (1) implementing a clinical warfarin dosing algorithm, (2) providing adherence support, (3) conducting root-cause analysis of warfarin-related adverse events, (4) implementing point-of-care INR testing, and (5) providing staff training. We anticipate that this warfarin bundle will be a cost-effective approach for better INR control compared to the current standard of care.

### Hypothesis

Our underlying hypothesis is that implementing a bundle of measures, including a clinical algorithm to guide individualized dosing of warfarin, will improve INR control and TTR in patients in Uganda and South Africa.

### Objectives

The primary objective of this study is to evaluate whether implementation of the warfarin bundle improves TTR. Secondary objectives include evaluating whether implementation of the warfarin bundle improves time to achieving a therapeutic INR or reduces the occurrence of adverse effects, assessing the acceptability of the bundle, exploring patients’ experiences, and estimating cost-effectiveness.

## Methods

### Study Design and Setting

This is a mixed methods implementation study of patient- and process-centered activities to improve the quality of anticoagulation in Sub-Saharan African patients involving 3 hospitals in Kampala, Uganda (Mulago National Referral Hospital, Uganda Heart Institute, and Kiruddu National Referral Hospital) and 2 hospitals in Cape Town, South Africa (Groote Schuur Hospital and Tygerberg Hospital).

The general study design is described in Figure 1.

**Figure 1 figure1:**
[figure not shown]
Study design highlighting prospective and retrospective components and outcomes. INR: international normalized ratio; TTR: time in therapeutic range.

### Patient Centered Components of the Warfarin Bundle

#### Implementing the Use of Dosing Algorithms

Participants of Black African ancestry will be dosed according to the warfarin dose initiation algorithm developed in our preceding study in Black African patients in Uganda and South Africa, which takes account of patient age, weight, target INR, and HIV status [6] (Multimedia Appendix 1). In South Africa, patients of other ethnicities will be initiated on warfarin using warfarin dosing algorithms which have already been published [7,8] (Multimedia Appendix 2). We will collaborate with their treating clinicians and calculate a warfarin initiation dose using the relevant algorithm.

Day 0 is considered the first day that warfarin is taken. We recruited participant up to 7 days before and no more than 1 day after warfarin was initiated, meaning some individuals may have taken a single warfarin dose. We will use a paper-based dosing table, using dose formulations currently available, which has been developed for implementation (Multimedia Appendix 1).

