### Sample Size and Power Calculations

To calculate our sample size, we assumed TTR in current practice to be 0.41 (based on average TTR from our audit) and the SD of TTR to be 0.25 on the basis that anticoagulation control before implementing the bundle is better than that found during the audit (0.33), due to the introduction of the clinical algorithm in a preceding pilot implementation study. We also assumed a Type I error rate of 0.05, power of 80%, and that the retrospective and prospective ratio would be 2:1. To achieve a minimum clinically important difference of 0.07 (ie, improvement from 43% to 50% TTR), we calculated that we would need at least 304 retrospective and 152 prospective participants (including a 10% contingency for losses to follow-up). This is in total across both Uganda and South Africa.

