### Participant Recruitment

#### Prospective Study

We will recruit participants for whom a decision has already been made to initiate warfarin by the managing clinician (Figure 2). Decisions regarding whether or not patients require inpatient management for the initiation of warfarin are also made by the managing clinician. Participants who meet the inclusion criteria will be consecutively screened and enrolled in the study. In cases where participants are discharged from the hospital and referred for follow-up in a clinic close to their home or in the outpatient clinic of the hospital, the clinical records used at the recruitment site and those at the referral clinic will be reviewed.

The participant’s first 3 days of dosing will be driven by our new algorithm (Multimedia Appendix 1). Thereafter, dose revisions will be made according to current guidance outlined in the “Standard Treatment Guidelines and Essential Medicines List for South Africa” [11]. We will repeat the INR of participants every 2-4 days until stability is reached (2 consecutive INRs are in the target range). We will ensure close monitoring during the first 14 days of treatment. If stability is reached before the 14th day, we will continue to closely monitor the patient for the first 14 days. If the participant has not reached stability at 14 days, we will continue to monitor the participant with INRs every 2-4 days and adjust the warfarin dose until stability is reached. As we measure participants’ INR every 2-4 days over this period of close follow-up, we will propose dose adjustments to the clinical team based on INR results. The clinical team will still be free to override proposed adjustments based on their clinical expertise. Once stability is reached, we will perform one more INR 1 week later, after which the participants’ care will be fully handed back to the clinical team, and participants will continue to follow-up according to the local standard of care. We will continue to monitor and record all consecutive INR results for 3 months through direct contact with the participant at outpatient clinic, home visits, or electronic or paper record review.

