**Figure 2 figure2:**
[figure not shown]
Flow diagram of prospective recruitment and follow-up. INR: international normalized ratio. War-PATH: Warfarin Anticoagulation in Patients in Sub-Saharan Africa.

**Table 1 table1:** Participant groups.

	Prospective	Retrospective
Population	Participants starting warfarin and consenting to implementation bundle	Historical controls started on warfarin at anticoagulation clinics where warfarin bundle is implemented
Sample size	152	330
Inclusion criteria	New initiators on warfarin Indication for warfarin is VTE^a^, AF^b^, or VHD^c^ Adults (ie, 18 years or older) Participant is resident in and willing to be followed up at a health facility where follow-up is feasible	New initiators on warfarin Indication for warfarin is VTE, AF, or VHD Adults (ie, 18 years or older)
Exclusion criteria	Pregnancy Received more than one dose of warfarin prior to recruitment Diagnosed with and currently on treatment for Tuberculosis	Pregnancy Diagnosed with and treated for Tuberculosis at time of warfarin initiation
Self-reported ethnicity	Yes	No
EQ-5D-3L questionnaire	Yes	No
Participant expenses tool	Yes	No
Baseline INR^d^	Yes	Yes
INRs during the first 3 months of treatment	Yes	Yes
All adverse events	Yes	Yes
Hospital admissions	Yes	Yes

^a^VTE: venous thromboembolism.

^b^AF: atrial fibrillation.

^c^VHD: valvular heart disease.

^d^INR: international normalized ratio.

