#### Retrospective Review of Patients’ Clinical Records

The following data will be collected from clinical records: age, sex, weight, indication for anticoagulation, target INR range, HIV status, recruitment center, all INR measurements during the first 3 months, any dose changes, and any hospitalizations or adverse events. If participants in the retrospective review were initially hospitalized and then discharged, the recruitment hospital site clinical records as well as the clinical records at the referral clinic will be reviewed.

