### Data Analysis Plan

For the prospective and retrospective studies, all statistical analyses will be undertaken in R. For determining percentage time in target range for each participant, all INR measurements during the first 12 weeks as well as the first INR measurement after the 12-week time point will be used, and the method of Rosendaal et al [14] will be applied. Percentage TTR will be compared between the prospective implementation group and the retrospective standard of care group using the Student *t* test. Time to achieving target INR (defined as the first of at least two INR measurements in range at the same dose) will be compared between the prospective and retrospective groups using the log-rank test (to compare the survival distributions of the 2 groups, and these will be calculated using the Kaplan-Meier estimator). Adverse events will be compared between the 2 groups using a chi-square test. A significance threshold of *P*<.05 will be applied.

The primary analysis will include all participants who remain in the project for at least 2 weeks (14 days). Our primary analysis will include only patients who have at least two weeks’ follow-up, since it is unlikely that those with less than 2 weeks’ follow-up will have sufficient information on INR measurements for TTR to be reliably estimated. A sensitivity analysis will be undertaken, including only participants who have completed 12 weeks (84 days) of follow-up.

We will also conduct both an intention-to-treat analysis (including all recruited patients) and a per-protocol analysis (excluding patients where health care provider decided to reject the dose recommended by the dosing algorithm). The project will follow national guidelines for best practice and be guided by local policy. Relevant data will be made openly available to other researchers in a timely way (after primary outputs are published) with as few restrictions as possible unless we are protecting intellectual property, respecting confidentiality, or honoring third-party agreements. The program management board will review access to data and will provide a governance mechanism.

We will perform a secondary analysis comparing the primary and secondary outcomes between retrospective controls from the pre–COVID-19 and COVID-19 periods to measure the impact of the pandemic on anticoagulation control.

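### The primary TTR comparison pools two countries with no balance or stratification by country, and ethnicity, which decides the starting algorithm in South Africa, is not collected for controls

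*Protocol article*

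**What the plan says.** **Size and comparison.** Sample Size and Power Calculations plans 304 retrospective and 152 prospective participants at 2:1 and adds: "This is in total across both Uganda and South Africa". No share per country is given. The Data Analysis Plan states the primary comparison: "Percentage TTR will be compared between the prospective implementation group and the retrospective standard of care group using the Student" *t* test. It names no stratification factor or covariate for TTR; regression on clinical and demographic factors appears only in the economic part. The Hypothesis is that the bundle "will improve INR control and TTR in patients in Uganda and South Africa". The Discussion describes a before-and-after design without concurrent control clinics.

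**Dosing.** Implementing the Use of Dosing Algorithms says: "Participants of Black African ancestry will be dosed according to the warfarin dose initiation algorithm developed in our preceding study in Black African patients". It continues: "In South Africa, patients of other ethnicities will be initiated on warfarin using warfarin dosing algorithms which have already been published". Under Prospective Study, after the first 3 days "dose revisions will be made according to current guidance outlined in the" South African standard treatment guidelines, with no distinction by country.

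**Data.** In Table 1 the row "Self-reported ethnicity" reads Yes for the prospective group and No for the retrospective group. The control data under Retrospective Review of Patients' Clinical Records are "age, sex, weight, indication for anticoagulation, target INR range, HIV status, recruitment center", followed by INRs, dose changes, hospitalizations and adverse events. Recruitment center is therefore recorded in both groups, and ethnicity in one only.

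**The concern.** Without randomization, the comparison is only as good as the similarity of the two groups. Country is an obvious way for them to differ: the health systems, clinics and usual care are not the same, and the bundle itself differs, since only South Africa uses more than one starting algorithm. If the share of Ugandan patients is not the same among bundle patients and controls, any difference in usual-care TTR between the countries enters the pooled difference as if it were an effect of the bundle. Nothing in the article prevents this, because the 2:1 ratio is a total and the test is unadjusted.

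Even with equal shares, the pooled figure is an average and does not show whether both countries named in the hypothesis gained. That matters because the findings are meant to inform a larger multisite trial.

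The ethnicity gap is of another kind. The plan treats ancestry as relevant to the starting dose in South Africa, but does not abstract it for controls. A later analysis plan can add country from the recruitment center; it cannot add a variable that was never collected.

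**Working it through.** **1. The plan's own figure.** Inputs from the sample size section: difference 0.07, SD 0.25, alpha 0.05 (taken as two-sided), power 80%, 2:1. With half as many prospective patients as controls, n(controls) = 3 × 0.25² × (1.960 + 0.842)² / 0.07² ≈ 301, with 151 prospective. The stated 304 and 152 match this only without the 10% contingency that they are said to include (with it: 335 and 168). That is a separate matter and does not affect this point. For 304 and 152, SE = 0.25 × √(1/152 + 1/304) = 0.0248, and power for 0.07 is about 80%.

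**2. What the pooled difference estimates.** Let p₁ and p₀ be the Ugandan shares among bundle patients and controls, μ the usual-care TTR and δ the bundle effect in each country (U, S):

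expected difference = p₁δ_U + (1 − p₁)δ_S + (p₁ − p₀)(μ_U − μ_S)

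The last term is bias. It vanishes if the shares are equal, which 2:1 selection within each country ensures, and stratifying by country removes it.

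**3. Size of the country term.** The documents give neither the shares nor TTR by country, so these are assumptions.
- Shares differ by 10 percentage points, TTR by 5 points: 0.10 × 5 = 0.5 points.
- Shares differ by 20 percentage points, TTR by 10 points: 0.20 × 10 = 2.0 points.
- Shares differ by 30 percentage points, TTR by 15 points: 0.30 × 15 = 4.5 points.

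The sign can go either way. With SE 2.48 points, the two-sided 5% error, 1 − Φ(1.96 − b/SE) + Φ(−1.96 − b/SE), becomes about 6.9%, 12.7% and 22.7% for a bias b of 1, 2 and 3 points.

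**4. What the average hides.** With equal halves, 14 points in one country and none in the other gives 0.5 × 14 + 0.5 × 0 = 7 points. The pooled test then has the same power, about 80%, as it has for 7 points in each.

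**5. Precision by country.** Assuming an even split (76 and 152) and SD 0.25, SE = 0.25 × √(1/76 + 1/152) = 0.0351, and the 95% half-width is 1.97 × 0.0351 = 0.069, or 6.9 points (9.1 with the audit SD of 0.33). Power for 7 points in one country is about 51%. Significance in both would have probability about 0.513 × 0.513 = 0.26.

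**6. Ethnicity in Cape Town.** Again by assumption only: a TTR gap of 5 to 15 points under the same care and a mix that shifts by 10 to 30 percentage points give 0.5 to 4.5 points within South Africa. If Cape Town is half of each group, that is 0.25 to 2.25 points overall.

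**7. Two passages side by side.** The algorithm section splits the starting algorithm by ethnicity. The Prospective Study section says that the first 3 days follow the new algorithm in Multimedia Appendix 1, with no such split.

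**The case against.** The strongest reply is that the article declares its target. Study Outcomes says that the comparison estimates the bundle as a whole and cannot separate its components. The starting algorithm is one component and covers 3 days of a 12-week measure. Giving each patient the relevant algorithm is part of the bundle, so mixed algorithms do not make the pooled effect meaningless. This stands.

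Second, the ethnicity bias is undocumented. The article supports ethnicity mattering for the starting dose; it does not show that TTR differs by ethnicity once doses are adjusted to INR, nor that the mix changed at the same clinics. This also stands, and the figures in step 6 show a possible range, no more.

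Third, country-specific reporting is often left to the analysis plan, and the hypothesis can be read as one about the combined population. Both are fair, so the lack of a country table is not in itself an error. But the article does fix the primary test as unadjusted and the ratio as a total, and it does decide not to collect ethnicity for controls.

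Two stronger readings are tempting. A reader might infer that the result cannot be read for the population for which the new algorithm was built. The documents do not support this: other algorithms are described for South Africa only and center is recorded in both groups, so a Ugandan contrast is available (that it largely concerns that population is an inference, as Uganda's ethnic mix is not stated). A reader might also take step 4 as a false-positive rate. It is not: if the average gain is 7 points, rejecting the pooled null is correct, and 80% is ordinary design power.

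**Conclusion.** The point holds in limited form. As fixed in the article, the primary comparison is open to bias from unequal country mix, and its pooled result alone cannot support a statement about each country. In Cape Town the groups can be neither compared nor adjusted on the characteristic that decides the starting algorithm. None of this overturns the whole-bundle comparison.

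The bias cannot be sized from the documents: the country term could be nil or, in the assumed range, a sizable part of the 7-point target. The ±7-point country interval assumes an even split, SD 0.25 and no losses. Because the country part can be removed with data already collected, the change should be made.

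**What to change.** 1. Select controls 2:1 within each country. If the control set is already fixed, stratify or adjust the primary TTR comparison by country, using recruitment center. This needs no new data and a few lines of analysis.
2. Report the TTR difference with its 95% CI for Uganda and for South Africa beside the pooled result, as description. Do not require significance in each country: at about 51% power apiece that rule would usually fail even if the target effect were present in both. The cost is wide intervals, to be shown as such.
3. Abstract recorded ethnicity for Cape Town controls where the notes hold it, amend the Table 1 entry to match, and use it in a sensitivity analysis of the South African groups. The cost is real: recruitment closed in August 2022 and analysis was under way by February 2023, so some charts, perhaps including referral-clinic records, may have to be reopened. An ethics notification under the existing waiver is possible. Ethnicity will be missing for some controls, and what notes record is not self-report.
4. Reconcile the algorithm section with the Prospective Study section on whether every participant's first 3 days follow the new algorithm, so that the intervention in each country is described in one way.
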